### Concealment mechanism {16b}

The allocation sequence will be performed by the evaluation team using RandList software. The randomization list will be accessible only to designated personnel within the project’s evaluation (internal) team of the Institute of Community Medicine (University Medicine Greifswald) and will be revealed after the baseline assessment is completed. All other study staff and investigators will have no access to the randomization list.

### Implementation {16c}

The allocation sequence will be performed by the Institute of Community Medicine (ICM) using RandList software.

## Assignment of interventions: blinding

### Who will be blinded {17a}

Study nurses capturing the outcomes will be blinded. However, due to the nature of the intervention, blinding is not feasible during the intervention period for Family Care Specialists and other staff of the memory clinic. Randomization will occur only after recruitment and baseline assessment are finalized. By maintaining concealment until this point, we mitigate potential selection bias and ensure that group assignment does not influence the initial evaluation of the dyads. Both caregiving experts and participating dyads will become aware of their group assignment once the intervention begins. As a result, the study is conducted with partial blinding, limited to the baseline assessment.

### Procedure for unblinding if needed {17b}

Not applicable.

#### Data collection and management

### Plans for assessment and collection of outcomes {18a}

After study inclusion, all participants will receive a baseline assessment using structured face-to-face interviews conducted by qualified study nurses, as well as caregiver self-assessments at the respective memory clinic. To comprehensively assess both individual and interactive aspects of caregiving, primary and crucial secondary supportive outcomes reflect the perspectives of both the PlwD and the informal caregiver. Follow-up assessment will be carried out 12 months after the baseline assessment in both study groups.

All study personnel involved in data collection have received intensive online training not only in data collection procedures, but also in communication with PlwD and their caregivers to ensure that the data collection process is not overly burdensome for participants and enable them to detect signs of distress and respond appropriately.

### Plans to promote participant retention and complete follow-up {18b}

Dyads in the intervention group will maintain frequent contact with the Family Care Specialists through home visits, phone calls, and messages via the app. The app will periodically prompt caregivers to complete brief questionnaires, and the caregiver’s reply will possibly trigger contact between the Care Specialist and the caregiver. Continuous access to the intervention and the mobile health app allows caregivers to seek timely support, advice and assistance, promoting engagement and sustained participation. The app’s interactive features—such as regular assessments and direct communication—are designed to foster commitment to the intervention and reduce attrition.

Dyads in the control group will receive a financial incentive (50 € per participant) for each completed baseline and follow-up interview. 

### Data management {19}

To ensure high data quality and completeness of data sets, multiple measures will be implemented during the study: before data entry, study nurses and Family Care Specialists receive comprehensive training on data handling and entry, using case examples and a test environment in the IMS software. At project initiation, a structured data monitoring system based on eCRFs within an IT-supported documentation platform will be established. This system employs intensive monitoring and key performance indicators to continuously ensure high data quality. Data management by a medical documentalist includes automated tasks, reminders for pending data collection, and systematic checks for completeness, quality, and plausibility. Any irregularities or missing data trigger feedback to study nurses and Family Care Specialists referring to participant IDs. This process ensures ongoing optimization of data collection. Additionally, designated contacts for data entry issues are communicated clearly to all study personnel at the start of the study. A regular coordination meeting (Jour Fixe) between the Family Care Specialists and the evaluation team facilitates early identification and resolution of data entry challenges as well as periodic retraining throughout the study.

### Confidentiality {27}

All data will be stored on secure servers, with personal identifiers kept separate from participants’ health information. Data storage complies with current standards for data security and privacy in accordance with the General Data Protection Regulation (GDPR). Only Family Care Specialists, study nurses, experts and other staff involved in the study (e.g., clinicians) will have access to personal data during baseline and follow-up assessments. An administrator will take care of the pseudonymization. All further study personnel will only get access to pseudonymized or aggregated data.

Paper documents (e.g., informed consent forms) will be securely stored and accessible only to authorized personnel. Access to the study software is protected by individual user passwords and a detailed rights and roles system, which emphasizes data minimization and security. Family Care Specialists and study nurses will only be able to view participant information relevant to their assigned memory clinic. All tablet PCs used for data collection are also secured with individual passwords.

### Plans for collection, laboratory evaluation and storage of biological specimens for genetic or molecular analysis in this trial/future use {33}

Not applicable.

## Statistical methods

### Statistical methods for primary and secondary outcomes {20a}

All data analyses will be conducted using pseudonymized datasets. Initially, all outcome variables will be subject to descriptive statistical analyses. At baseline, the intervention and control groups will be compared regarding significant differences, serving as a randomization check. If notable differences are identified, all subsequent analyses will be adjusted for the respective factors. After completing the assessment, we will conduct a drop-out analysis using multivariate logistic regression to evaluate any systematic differences between included and excluded patients.

For the primary outcome, an ordinal logistic regression (proportional odds model) will be used to analyze the full six-category ordinal scale PTS. The intervention effect on the secondary outcomes will be evaluated using multivariate linear and logistic regression models, adjusted for age, sex, and living situation (alone vs. together with the caregiver), and including random effects for the respective memory clinic to account for clustering. The different study sites will be treated as clusters in these analyses. The analyses will be done on intention-to-treat (base case analysis) and per-protocol analyses (sensitivity analysis).

For the health-economic evaluation, the incremental cost-effectiveness ratio (ICER) will be calculated by comparing the additional cost per QALY gained through the intervention. Nonparametric bootstrapping resampling will be used to account for sample uncertainty in the ICER estimates. Various willingness-to-pay thresholds will be applied to determine probabilities of cost-effectiveness.

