## Assignment of interventions: allocation

### Sequence generation {16a}

The randomization will be conducted by the University Medicine Greifswald, Institute for Community Medicine using RandList software (Version 2, Datinf, Germany). Eligible dyads will be randomly assigned in a 1:1 ratio to the intervention or control group using computer-generated block randomization at the level of the memory clinics to ensure the parallelism of sampling, even in the case of under-recruitment. The clinics will receive the randomization lists in blocks of six.

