### Methods for additional analyses (e.g., subgroup analyses) {20b}

Quantitative outcomes within subgroups will be analyzed using multivariate linear and logistic regression models. If differences between the intervention and control groups are observed at baseline, adjustments will be made for relevant covariates such as age, gender, and dementia severity. In addition to intention-to-treat analyses, per-protocol analyses will be conducted with participants who actually received the intervention. Further analyses will focus on specific subgroups of the study population, for example based on dementia severity or variations in home care settings.

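### The primary model's covariates depend on chance baseline differences between randomised arms, and no analysis names baseline PTS as a covariate

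*Protocol article*

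**What the plan says.** All references are to the protocol article.

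- **Baseline comparison, Statistical methods {20a}.** "At baseline, the intervention and control groups will be compared regarding significant differences, serving as a randomization check". The consequence follows at once: "If notable differences are identified, all subsequent analyses will be adjusted for the respective factors". The variables to be compared are not listed, and nothing says what makes a difference notable.
- **Primary model, same section.** "For the primary outcome, an ordinal logistic regression (proportional odds model) will be used to analyze the full six-category ordinal scale PTS". No covariate is named in that sentence.
- **Secondary models, same section.** These have a fixed list: "adjusted for age, sex, and living situation (alone vs. together with the caregiver), and including random effects for the respective memory clinic". The next sentence treats the sites as clusters, but does not make clear whether it refers to the secondary models alone or to the primary model as well.
- **Additional analyses {20b}.** Adjustment is again conditional on observed baseline differences: "adjustments will be made for relevant covariates such as age, gender, and dementia severity".
- **Sequence generation {16a}.** Allocation uses "computer-generated block randomization at the level of the memory clinics", so clinic is the randomisation stratum.
- **Outcomes {12}.** Primary and secondary outcomes are measured at baseline and at 12 months, so a baseline PTS value is planned for every dyad.

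**The concern.** The only covariate rule that clearly reaches the primary analysis is triggered by the data. Three things follow.

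1. **The trigger selects the wrong variables.** With proper randomisation, any baseline difference is due to chance. A significance test measures how large that chance difference is, not whether the variable predicts month-12 PTS. A strong predictor that happens to be balanced is left out, and an irrelevant variable that happens to be unbalanced is put in.
2. **The model is not fixed.** Without a threshold or a list of variables, two analysts could follow the text and fit different primary models.
3. **The estimated quantity moves.** Odds ratios are non-collapsible: a proportional odds estimate conditional on prognostic covariates differs from the unconditional one even when the arms are perfectly balanced. Changing the covariate set changes what is reported, not only its standard error.

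There is also an efficiency cost. Baseline PTS can be expected to be among the best predictors of PTS at 12 months, and the article does not say that it will be used.

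**Working it through.** **Step 1. The plan's own figure.** Inputs from Sample size {14}: 23% against 35%, 80% power, α = 0.05, chi-square test. The two-sided formula with pooled variance and no continuity correction gives 224 per group, as stated. Then 224 / (1 − 0.175) = 271.5, rounded up to 272, also as stated. This calculation uses no covariates, so leaving out baseline PTS does not invalidate it.

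**Step 2. How often chance would trigger the rule.** For k independent baseline variables tested at 5%, P(at least one significant) = 1 − 0.95^k. The article gives neither k nor the level, so both are assumptions.

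| k | 1 − 0.95^k |
|---|---|
| 5 | 23% |
| 10 | 40% |
| 20 | 64% |

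**Step 3. What baseline PTS could contribute.** The article gives no baseline to month-12 correlation r, so a range is used. Under a linear approximation, adjustment removes a share r² of the residual variance: 0.3² = 9%, 0.5² = 25%, 0.6² = 36%.

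**Step 4. Power at 196 per arm.** This is 272 × (1 − 0.28) = 195.8, using the plan's total loss including death. The effect is a shift on a latent normal scale that moves the share at 12 months or more from 23% to 35%. Category splits are assumed, and the test is rank-based analysis of covariance (3,000 simulated trials).

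| r (assumed) | Unadjusted | Adjusted for baseline PTS |
|---|---|---|
| 0.3 | about 91–92% | about 94% |
| 0.5 | about 91–92% | about 96% |
| 0.6 | about 91–92% | about 98% |

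A hand check supports the scale. The latent shift is Φ⁻¹(0.77) − Φ⁻¹(0.65) = 0.739 − 0.385 = 0.354. If the latent variable were observed directly, power would be Φ(0.354 × √(196/2) / √(1 − r²) − 1.96). That is Φ(1.54) = 93.8% at r = 0, and 95.6%, 98.1% and 99.2% at r = 0.3, 0.5 and 0.6. Grouping into six categories costs a little, which fits the simulated values.

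The unadjusted figure exceeds 80% because the whole scale is used and the shift is assumed to be the same across it. It is not a re-estimate of the chi-square power.

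**Step 5. Sensitivity to a smaller effect.** A proportional odds simulation at 224 per arm (400 runs per r, assumed category splits) used a log odds ratio of 0.42. Power rose from 0.72 to 0.78 at r = 0.3, from 0.69 to 0.81 at r = 0.5, and from 0.71 to 0.91 at r = 0.7. The plan's proportions imply a larger effect: ln[(0.35/0.65)/(0.23/0.77)] = ln 1.80 = 0.59. A log odds ratio of 0.42 takes 23% only to about 31%. These larger gains therefore show what happens if the true effect falls short, and should not be used to size the point under the plan's own assumption.

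**Step 6. Type I error.** A null simulation had 196 per arm, a continuous outcome, and adjustment for every baseline variable with p < 0.05. It gave 4.4% (20 variables, covariate R² 0.3), 4.9% (20 variables, R² 0) and 4.4% (10 variables, R² 0.3). A mechanical version of the rule does not inflate the error rate. The simulation does not cover an analyst's judgement of what counts as notable.

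**The case against.** The strongest reply is that this is a condensed article. It gives the primary analysis one sentence, and a covariate list is the kind of detail usually left to the full protocol or the analysis plan. That reply stands for the list: the article does not say that the primary model is unadjusted, only that no covariate is named. It does not rescue the test-and-adjust rule. That rule is stated outright for all analyses, and an analysis plan could remove it only by contradicting the article.

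A second reply is that the efficiency gain is modest and rests on assumed inputs. That also stands. Under the plan's effect the gain is roughly 2 to 7 points, from a starting power already above 80%.

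A reader might also infer more than the text supports:

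- **That the primary model has no clinic term.** The site-as-cluster sentence may extend to the primary, since the sentence after it, on intention-to-treat and per-protocol analysis, evidently does. Only ambiguity is shown.
- **That {20b} contradicts {20a} on covariates.** The {20b} list is illustrative and concerns additional analyses, so it may differ. What the two sections share is the conditional trigger.
- **That the rule inflates type I error.** Nothing in the article shows this, and step 6 found no inflation for a mechanical rule.
- **That the sample size is wrong.** It reproduces.

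**Conclusion.** The point holds as a recommended change. It does not threaten the trial's validity. The adjustment rule in {20a} is badly fixed: it reaches the primary analysis, selects covariates by chance imbalance, has no threshold, and leaves the primary odds ratio undefined until the data are seen. That conclusion rests on the text alone.

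The numbers are illustrative. The 40% to 64% chance of a trigger assumes 10 to 20 independent tests at 5%. The rise from about 91–92% to about 94%, 96% or 98% power assumes correlations of 0.3, 0.5 or 0.6, particular category splits and 196 dyads per arm. Baseline PTS is not named in the article as a covariate, and the reach of the clinic term is unclear. Neither is proved absent from the full analysis plan.

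**What to change.** 1. In {20a}, delete the baseline testing and the adjustment that depends on it, and delete the conditional adjustment in {20b}. Keep baseline tables as description only.
2. State the primary proportional odds model in full: arm, baseline PTS (say whether as categories or as a score), memory clinic (fixed or random, decided in advance), age, sex and living situation. If dementia severity is wanted, add it to the fixed list now.
3. For each secondary outcome, keep the existing list and add that outcome's own baseline value.
4. Say explicitly whether the sentence on sites as clusters applies to the primary model.

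The cost is wording in the protocol and analysis plan, plus the notice to ethics committees and the registry update that the protocol's section {25} already foresees. Baseline PTS and clinic need no new data item, because baseline assessments are already scheduled. Recruitment began in January 2026 and follow-up is at 12 months, so the first month-12 outcomes fall due around January 2027. The list should be fixed before then, or at the latest before any comparison by arm.

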#### Further secondary outcomes

A secondary outcome of the study is the caregiver’s resilience, measured by the Resilience and Strain Questionnaire in Caregivers of People with Dementia (ResQ-Care-Dem) questionnaire, which consists of four scales with five items each. Two scales (“My inner attitude” and “My sources of energy”) assess resilience [32, 33]. The other two (“Difficulties in managing the person with dementia” and “General burdens of my living situation”) assess perceived burden. The instrument creates different profiles based on the ratio of burden and resilience factors.

To measure objective stress, hair samples will be analyzed by the University of Konstanz in collaboration with the University of Vienna to assess hair cortisol concentration in caregivers and PlwD, providing a physiological marker of chronic stress [34]. For this analysis, the study nurse will collect two strands of hair from each participant’s back of the head (posterior vertex) at baseline and 12 months later. The strands together should have a diameter of half a pencil, a length of at least 3 cm, and they should be cut as close to the scalp as possible. In addition, information regarding the participant’s hair (e.g., natural color, hair treatments, washing frequency) will be collected via questionnaire. If participants do not consent to the capturing of a hair sample or if their hair is shorter than 3 cm, no samples will be taken.

Another secondary outcome is the caregiver’s self-efficacy measured with the CSES-8 [35]. Self-efficacy means the strength of the caregiver’s belief in being able to complete a specific task. It is a modifiable trait, making it a valuable secondary outcome. The instrument creates a mean score of eight items, with higher scores indicating greater confidence in one’s own caregiving abilities.

A high caregiver burden, less resilience factors and low self-efficacy can lead to depression or anxiety symptoms [36]. Thus, these symptoms will be screened using short versions of the Patient Health Questionnaire (PHQ-2) and the Generalized Anxiety Disorder (GAD-2) tool. Both instruments yield sum scores between 0–6, with ≥ 3 indicating the likely presence of the respective disorder.

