### Limitations

A notable limitation of this study is the lack of participant and caregiver blinding, which is often unavoidable in complex psychosocial real-life interventions. This open-label design introduces a risk of performance and detection bias, as caregivers in the intervention group were aware of the additional support provided by the app and Family Care Specialists. Such awareness may result in a positive reporting bias (Hawthorne effect) [45], where participants might overestimate their perceived resilience (PTS) or underestimate their burden (ZBI) due to social desirability or high expectations. We estimate the potential magnitude of this bias to be moderate.

To mitigate this risk and ensure the robustness of our findings, we employed a triangulation strategy. By integrating objective secondary outcomes—specifically physiological hair cortisol levels as a marker of chronic stress and health insurance claims data to track the progression of care levels—we provide an empirical counterweight to the self-reported measures. The alignment of these objective parameters with subjective assessments allows for a more reliable interpretation of the intervention’s true clinical impact, reducing the likelihood that the observed effects are merely a result of reporting artifacts. 

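### The covariates fixed for hair cortisol leave out its baseline value and the hair characteristics the trial collects, which gives away precision on its one objective marker in randomized dyads

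*Protocol article*

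**What the plan says.** Protocol article, Statistical methods for primary and secondary outcomes {20a}: the intervention effect on secondary outcomes is to be "evaluated using multivariate linear and logistic regression models, adjusted for age, sex, and living situation (alone vs. together with the caregiver"), "including random effects for the respective memory clinic to account for clustering". The same section has a conditional rule after the baseline comparison of the arms: "If notable differences are identified, all subsequent analyses will be adjusted for the respective factors". Section {20b} repeats the rule for additional analyses: if the arms differ at baseline, "adjustments will be made for relevant covariates such as age, gender, and dementia severity". No hair characteristic is among its examples.

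Under Further secondary outcomes, samples are taken "to assess hair cortisol concentration in caregivers and PlwD, providing a physiological marker of chronic stress". They are taken "from each participant’s back of the head (posterior vertex) at baseline and 12 months later", so a baseline concentration exists for those who give a sample. In addition, "information regarding the participant’s hair (e.g., natural color, hair treatments, washing frequency) will be collected via questionnaire". The article gives these hair data no use in the analysis. It also does not say whether cortisol is analysed raw or log-transformed, or as a follow-up value or a change.

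Under Limitations, two objective measures are to offset reporting bias: claims data and "specifically physiological hair cortisol levels as a marker of chronic stress".

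**The concern.** The covariate list is explicit, and hair cortisol is among the outcomes it covers. The trial goes to the trouble of measuring cortisol at baseline and recording hair characteristics, yet the stated model uses neither unless a chance imbalance brings them in. A covariate's precision gain depends on how well it predicts the outcome, not on whether the arms happen to differ on it. If the arms are balanced on baseline cortisol, the rule in {20a} leaves it out and the whole gain is lost. The rule also makes the final model depend on the data.

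This matters more for cortisol than for most secondary outcomes. The Limitations section rests its answer to the lack of participant blinding on agreement between objective and self-reported results. The section Claim data analysis says the insurer data are analysed separately, without individual linkage, and compare people treated at memory clinics with people treated elsewhere. They cannot show a difference between the randomized arms. Of the two named counterweights, that leaves cortisol. Sampling is optional (section {26b}) and needs at least 3 cm of hair, so fewer people will contribute than complete follow-up, and precision should not be given away.

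**Working it through.** **Inputs from the Protocol article.** 272 dyads per arm and 28% total loss including death (Sample size {14}); hair sampled at baseline and month 12; sampling optional, uptake not given.

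**Inputs assumed, because the article gives none.** Correlation r between baseline and month-12 cortisol, given the covariates already planned: 0.2 to 0.7. Share h of variance explained by hair factors beyond baseline cortisol: 0 or 10%. Uptake: 100% or 50%. True difference for the power illustration: 0.25 SD. Log-SD of cortisol: 0.3 to 1.0.

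**1. The plan's own figures.** For 23% versus 35%, two-sided 5%, 80% power, pooled proportion 0.29:

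n = [1.960·√(2·0.29·0.71) + 0.842·√(0.23·0.77 + 0.35·0.65)]² / 0.12² = (1.258 + 0.535)² / 0.0144 = 223.3, so 224 per arm.

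224 / (1 − 0.175) = 271.5, so 272. Both match. They concern the dichotomized Perseverance Time Scale. No design figure is given for cortisol, so they neither support nor weaken this point.

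**2. Precision.** Standard error with the extra covariates, relative to without, is √(1 − r² − h). For r = 0.5 and h = 0 this is √0.75 = 0.866, a 13% reduction.

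**3. Power.** Evaluable per arm: 272 × 0.72 = 195.8, taken as 195 at full uptake; about 97 at half uptake. Power = Φ(0.25 / [√(2/n)·√(1 − r²)] − 1.96). At n = 195 without the covariate: 0.25 / 0.1013 = 2.469, and Φ(0.509) = 69%. With r = 0.5: 2.469 / 0.866 = 2.851, and Φ(0.891) = 81%.

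| r | SE reduction, baseline only | SE reduction, plus h = 10% | Power, 195 per arm, baseline only | Power, 97 per arm, baseline only |
|---|---|---|---|---|
| not used | – | – | 69% | 41% |
| 0.2 | 2% | 7% | 71% | 43% |
| 0.3 | 5% | 10% | 73% | 45% |
| 0.4 | 8% | 14% | 77% | 48% |
| 0.5 | 13% | 19% | 81% | 52% |
| 0.6 | 20% | 26% | 87% | 59% |
| 0.7 | 29% | 36% | 93% | 68% |

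The gain is small at low correlation and becomes substantial from about r = 0.5. The 10% column is generous: hair habits that stay the same over the year are already partly reflected in baseline cortisol.

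**4. Scale.** If the outcome is log-normal with log-SD s, a raw-scale comparison has efficiency s² / (exp(s²) − 1) relative to the log scale for small effects: 0.96, 0.88, 0.78 and 0.58 for s = 0.3, 0.5, 0.7 and 1.0. This shows why the scale should be named. It is not a loss the article incurs, since the article names no scale.

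**5. Would a real effect probably be missed?** Take the unfavourable case of a raw-scale analysis without baseline, and assume a true 25% reduction. The standardized difference is d = 0.25 / √[(exp(s²) − 1)(1 + 0.75²)/2], which is 0.356 for s = 0.7 and 0.216 for s = 1.0. Power is Φ(d·√(n/2) − 1.96). At s = 0.7 and 196 per arm it is Φ(1.56) = 94%. At s = 1.0 and 98 per arm it is Φ(−0.45) = 33%. The answer turns entirely on the assumptions.

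**The case against.** The strongest reply is that {20a} is one generic sentence for all secondary outcomes in a condensed article. Transformations and assay covariates for an optional biomarker are commonly left to the statistical analysis plan, which is not shown. The oversight section also assigns the hair cortisol analyses to a separate partner, although that may mean laboratory work only. This reply largely disposes of any complaint about scale; what remains there is a request to state it. It weighs less on the covariates, because the article does not leave them open. It gives a named list and a rule for extending it, and that rule does not secure the gain.

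Two further objections stand. First, the stated model is more than three covariates: it has a clinic random effect, and baseline cortisol or a hair factor could enter if the arms differed on it. Second, hair factors recorded at month 12 are measured after randomization. Personal hygiene is one of the need domains in the unmet-needs instrument, and the intervention targets unmet needs, so washing frequency could itself be affected by the arm. Adjusting the main analysis for month-12 values would therefore be unsafe.

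A reader might also infer that cortisol will be analysed untransformed. The text does not support this: linear names the type of model, and a log-transformed outcome is fitted by linear regression too.

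**Conclusion.** The point holds as a matter of precision. The fixed adjustment set leaves out baseline cortisol and the collected hair characteristics, and adjustment triggered by observed imbalance is no substitute. Under assumed correlations of 0.2 to 0.7, baseline cortisol alone would lower the standard error by about 2% to 29%; with a further assumed 10% of variance from hair factors, by about 7% to 36%.

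Three stronger conclusions are tempting and not supported. That the marker loses much of its precision cannot be shown, because the article gives no cortisol SD, skewness, correlation, hair-factor contribution or uptake. That a real effect is likely to be missed holds in only part of the plausible range (step 5). That the result would be biased is wrong: in a randomized comparison, leaving out a baseline predictor does not by itself bias a linear-model estimate. Nor does the article set a rule under which a null cortisol result counts as evidence of reporting bias; that misreading is a risk, not a stated plan.

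Cortisol is a further secondary outcome with no power claim, so nothing in the main conclusion of the trial depends on this. It is worth correcting because the gain comes from data already being collected.

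**What to change.** For hair cortisol, prespecify:

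- log month-12 concentration as the outcome, with the arm effect reported as a ratio of geometric means;
- log baseline concentration as a covariate, whether or not the arms differ on it;
- hair treatment, washing frequency and natural colour as recorded at baseline;
- age, sex, living situation and the clinic effect as already planned;
- separate models for caregivers and for persons with dementia;
- month-12 hair factors in a sensitivity analysis only, because they are post-randomization.

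The plan should also say how people with a month-12 sample but no baseline sample are handled.

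The change needs no new data. It costs a few degrees of freedom and a result expressed as a ratio instead of a difference in concentration.
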